### Concomitant therapy

Sites will follow the 2020 European Respiratory Society guidelines for the treatment of chronic cough.^6^ During the 6-week randomised phase, use of morphine, pregabalin and non-pharmacological cough interventions outside of the allocated treatment will generally not be permitted to avoid confounding. During this phase, patients will also not be allowed to co-enrol in other clinical trials involving investigational medicinal products for the treatment of RCC/UCC.

Patients who do not respond to their allocated treatment (morphine or pregabalin) will not be permitted to switch to the other neuromodulator or alternative antitussives (eg, gabapentin, amitriptyline, codeine, dextromethorphan) during the 6-week randomisation period. This is to preserve the integrity of treatment allocation and minimise treatment contamination.

Once patients complete the 6-week randomised phase and enter the observational extension, patients can take any concomitant treatments, including switching neuromodulators, engaging in adjunctive therapies or enrolling in other clinical trials of RCC/UCC. We will closely monitor and document therapies taken during the observational extension for up to 1 year.

### Study treatment adherence

We will assess adherence to morphine and pregabalin by self-report and tablet count. The physiotherapist and speech-language pathologist will evaluate adherence to CCT via the number of attended sessions and through weekly adherence diaries.^24^ For participants receiving the PRN bowel regimen, we will record the number of doses taken since the previous visit.

### Study outcomes

#### Primary effectiveness outcome (randomised phase)

For the comparison between morphine versus pregabalin, and CCT versus no CCT, we will evaluate:

The change from baseline in 24-hour cough frequency (coughs/hour) measured by the VitaloJAK ambulatory cough monitor at 6 weeks.

#### Secondary effectiveness outcomes (randomised phase)

For the comparison between morphine versus pregabalin, and CCT versus no CCT, we will evaluate:

The change from baseline in awake cough frequency (coughs/hour) measured by the VitaloJAK ambulatory cough monitor at 6 weeks.The change from baseline in sleep cough frequency (coughs/hour) measured by the VitaloJAK ambulatory cough monitor at 6 weeks.The change from baseline in cough bouts (defined by inter-cough intervals) measured by the VitaloJAK ambulatory cough monitor at 6 weeks.The change from baseline in cough severity on the McMaster Cough Severity Questionnaire (MCSQ) at 6 weeks.The change from baseline in cough severity on the 100-mm VAS at 6 weeks.The change from baseline in cough-specific quality of life on the LCQ at 6 weeks.The proportion of patients achieving a ≥30% reduction in 24-hour cough frequency at 6 weeks.The proportion of patients achieving a ≥30 mm reduction on the 100-mm CS-VAS at 6 weeks.The proportion of patients achieving a ≥1.3-point improvement on the LCQ at 6 weeks.

#### Secondary effectiveness outcomes (observational extension phase)

The change from week 6 (end of randomised phase) in cough severity on the MCSQ at 6 and 12 months.The change from week 6 (end of randomised phase) in cough severity on the 100-mm VAS at 6 and 12 months.The change from week 6 (end of randomised phase) in cough-specific quality of life on the LCQ at 6 and 12 months.

#### Safety outcomes

The proportion of patients with any adverse event (AE) for each intervention at 6 weeks, 6 months and 12 months.The proportion of patients with treatment-related AEs for each intervention at 6 weeks, 6 months and 12 months.The proportion of patients with serious adverse events (SAEs) for each intervention at 6 weeks, 6 months and 12 months.The proportion of patients with AEs leading to treatment discontinuation for each intervention at 6 weeks, 6 months and 12 months.

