**Figure 1 F1:**
[figure not shown]
FORTITUDE study design. BID, two times per day; CS-VAS, Cough Severity Visual Analogue Scale; EQ-5D-5L, EuroQol-5 Dimensions-5 Instrument; FORTITUDE, *F*act*O*rial *R*andomized *T*r*I*al *T*o eval*U*ate neuromo*D*ulators and cough control th*E*rapy; LCQ, Leicester Cough Questionnaire; MCSQ, McMaster Cough Severity Questionnaire; PGIC, Patient Global Impression of Change Instrument.

Following the 6-week randomised period, participants will enter a 1-year observational extension with assessments at 6 and 12 months. Participants will not be required to remain on their randomised treatment, allowing us to examine real-world long-term effectiveness, treatment trajectories, tolerability and CCT uptake.

This trial will adhere to the 2025 Consolidated Standards of Reporting Trials (CONSORT),^19^ the Factorial Randomized Trials Extension^20^ and the 2025 Standard Protocol Items: Recommendations for Interventional Trials (SPIRIT) guidelines.^21^ The trial is registered on ClinicalTrials.gov (NCT07288528). Online supplemental files 1–3 include the Trial Structured Summary, the completed 2025 SPIRIT checklist and the Informed Consent Form. The estimated trial period is September 2026 to September 2029.

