### Analysis of safety outcomes

We will report all safety outcomes descriptively according to the as-treated population. The as-treated population will include analysing those based on the treatment received, regardless of their initial randomisation. During the randomised phase, AE categories—including participants with any AE, treatment-related AEs, SAEs and discontinuation due to AEs—will be reported descriptively at 6 weeks. AEs occurring in ≥10% of participants in a single group at 6 weeks will be highlighted. In addition, we will specifically monitor and report the incidence of the most common side effects of each study drug. For morphine, this includes constipation and drowsiness/sedation. For pregabalin, this includes dizziness, somnolence and peripheral oedema. Safety outcomes during the observational extension will be similarly reported based on participants’ treatment exposure at 6 and 12 months.

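### The 6- and 12-month safety proportions ignore time on drug, so they may not be comparable between drugs; the direction of any distortion depends on how patients and events are assigned

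*Protocol article*

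**What the plan says.** Under Safety outcomes, the Protocol article lists four measures: any adverse event, treatment-related events, serious events and events leading to discontinuation. All have the same form, for example "The proportion of patients with any adverse event (AE) for each intervention at 6 weeks, 6 months and 12 months" and "The proportion of patients with serious adverse events (SAEs) for each intervention at 6 weeks, 6 months and 12 months". The form is identical for the randomised phase and the extension.

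Under Trial design, once week 6 has passed, "Participants will not be required to remain on their randomised treatment". Under Concomitant therapy, "patients can take any concomitant treatments, including switching neuromodulators, engaging in adjunctive therapies or enrolling in other clinical trials of RCC/UCC". The same section promises: "We will closely monitor and document therapies taken during the observational extension for up to 1 year".

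Under Analysis of safety outcomes, "We will report all safety outcomes descriptively according to the as-treated population", and the set is defined thus: "The as-treated population will include analysing those based on the treatment received, regardless of their initial randomisation". For the extension, "Safety outcomes during the observational extension will be similarly reported", with participants grouped by the treatment they are exposed to at the two extension timepoints. This rule assigns patients to treatments. It gives no time-at-risk denominator, no risk window after stopping, and no statement of which drug carries an event in a patient who switched.

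**The concern.** In the first 6 weeks switching is barred and follow-up is short, so a proportion is a fair summary, although patients can still stop. From week 6 to month 12 one drug may be kept for most of the period and the other dropped early. A proportion of patients with an event rises with time at risk, and it also depends on who is still counted under a drug. Two drugs with the same event rate can therefore show different percentages.

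The Abstract names long-term safety as a purpose of the extension, and the Discussion cites the lack of head-to-head evidence on long-term harms. Readers will set the two percentages side by side even though no test is planned.

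**Working it through.** **The plan's own figures.** The documents give no adverse event rate, stopping rate or exposure time, so there is no safety figure to reproduce. The sample size (d = 0.357/0.6, two-sided alpha 0.025, 80% power: 55 per group; 55/0.9 = 61.1, so 62 per group and 124 in total) reproduces, but it concerns cough frequency and has no bearing here.

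**Assumed inputs.**
- Extension length T = 12 months − 6 weeks ≈ 10.6 months.
- The same constant first-event rate λ on both drugs: 5% or 10% per month.
- A constant stopping rate μ for reasons other than adverse events: 5% per month on drug A, 15% or 20% on drug B.
- Mean time on drug = (1 − e^(−μT))/μ, which is 8.2, 5.3 and 4.4 months for μ = 5%, 15% and 20%.

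**Reading 1: on-drug events over everyone who took the drug.** P = λ/(λ+μ) × (1 − e^(−(λ+μ)T)).
- λ = 5%, A: 0.05/0.10 × (1 − e^(−1.06)) = 32.7%. B at 15%: 0.05/0.20 × (1 − e^(−2.12)) = 22.0%.
- λ = 10%, A: 0.10/0.15 × (1 − e^(−1.59)) = 53.1%. B at 15%: 0.10/0.25 × (1 − e^(−2.65)) = 37.2%.
- B at 20%: 18.6% (λ = 5%) or 31.9% (λ = 10%), against the same A figures.

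The drug with better persistence looks worse by 11 to 21 percentage points, although the true rates are equal.

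**Reading 2: patients grouped by the drug they are on at month 12.** Let q be the share of patients with a first event who stop because of it. Among those still on the drug, P = (1 − e^(−λT))(1 − q) / [(1 − e^(−λT))(1 − q) + e^(−λT)]. Stopping for other reasons cancels out.
- λ = 5%, q = 0 on both drugs: 1 − e^(−0.53) = 41% versus 41%, despite mean exposure of 8.2 versus 5.3 months. The distortion vanishes.
- λ = 5%, q = 0.6 on A and 0 on B: A = 0.411 × 0.4/(0.411 × 0.4 + 0.589) = 22%, B = 41%. Mean exposure on A is 0.4 × 8.2 + 0.6 × (1 − e^(−1.06))/0.10 = 7.2 months, against 5.3 on B. The longer-used drug now looks safer.
- A simulation at one event per patient-year over 12 months shows the same pattern: 63% versus 63% with q = 0, and 41% versus 63% with q = 0.6 on A only (mean exposure 8.5 versus 6.2 months).

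Under this reading the fourth outcome nearly empties. A patient who stopped a drug because of an adverse event is, unless restarted, no longer in that drug's group at the visit.

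**Reading 3: starting group kept, all events to month 12 counted.** At one event per patient-year, simulation gives 63% versus 63% if the rate off drug equals the rate on drug, and 61% versus 52% if it is half. This reading fits the as-treated definition least well.

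**Effect of a time-based measure.** Patient-time to first event, stop or end of follow-up is (1 − e^(−(λ+μ)T))/(λ+μ). Dividing the Reading 1 proportion by it returns λ exactly. At λ = 5%, A gives 0.327/6.54 months and B gives 0.220/4.40 months, both 5 per 100 patient-months.

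**The case against.** A reader might infer that the drug patients stay on longer is bound to look more harmful. The documents do not support that. It follows only under Reading 1, and the article's rule of grouping by exposure at the extension timepoints can be read as Reading 2, where the distortion vanishes or reverses.

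Other points against the concern have weight. Every rate above is assumed. With at most 62 patients per drug, a 95% interval is about ±16 points around 33% versus 22%, and about ±17 around 53% versus 37%, so such differences would be hard to tell from chance. The safety analysis is descriptive, with no test. The Strengths and limitations box and the Discussion concede that the extension cannot support causal comparison. The descriptive analyses at 6 and 12 months will show who continues, switches or stops, and why. The article refers to a supplementary analysis plan that is not shown and may contain exposure-adjusted rates.

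These points limit the importance of the concern but do not remove it. The conceded limitations are confounding and selection bias; unequal time at risk is a separate problem that the data can address. Counts of continuers and switchers do not give time on drug. The point rests on a measure that the article states, not on detail left to another document.

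**Conclusion.** The concern holds in a limited form. The extension safety outcomes are plain proportions, time on each drug may differ freely after week 6, and the stated grouping rule does not account for it. The proportions may therefore not be comparable between drugs even at equal event rates. Under the assumed rates the artefact runs from 11 to 21 points against the longer-used drug (Reading 1), through zero, to about 19 points in its favour (22% versus 41%, Reading 2 with stopping driven by adverse events on that drug). No direction can be claimed from the documents. The 6-week safety figures are much less affected, and neither the primary analysis nor the sample size is touched. This is a worthwhile, low-severity improvement.

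**What to change.** Keep proportions for the 6-week phase. For week 6 to month 12, amend Safety outcomes and Analysis of safety outcomes as follows:

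- Assign each event to the drug being taken when it occurred.
- For each drug, report duration of exposure and the number of patients with a first event in that period per 100 patient-months on drug, with a confidence interval, split at 6 months. Count time from the later of week 6 or drug start to first event, drug stop or last contact. An event in the randomised phase does not remove a patient from this count.
- For discontinuation due to adverse events, report cumulative incidence since drug start, with stopping for other reasons as a competing event.
- Show the proportions only beside the exposure.

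The cost is a few sentences and modest programming. Drug start and stop dates must be recorded explicitly: the therapy documentation promised under Concomitant therapy implies them but does not name them. Rates assume a roughly constant hazard within each period, and the split at 6 months eases this only in part. Rates also do not remove the confounding that the Discussion concedes.

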### Visit schedule

Trained research staff will perform all study visits. The study has in-person and telephone visits, with electronic administration of all patient-reported outcome measures on REDCap in English and French. Online supplemental file 4 provides a summary of the visits.

### Outcome measures

#### 24-hour cough monitoring with VitaloJAK

An ambulatory cough monitor (VitaloJAK, Vitalograph, UK) will quantify the number of coughs over a 24-hour period. The VitaloJAK cough monitor consists of an air microphone on the lapel, a chest sensor on the sternum and a battery-operated device around the waist.

The monitor captures audio at 8 kHz and 16-bit waveform format. A study coordinator will transfer recordings to a password-protected and encrypted server, where validated, custom-written software will remove silence and background noises. Outputs include 24-hour, awake and sleep cough frequency expressed as coughs/hour. Cough bouts, defined as more than one cough occurring with inter-cough intervals of 3–10 s,^25^ will be explored as a secondary endpoint.

### Patient-reported outcome measures

#### McMaster Cough Severity Questionnaire

The MCSQ is an 8-item instrument that assesses patients’ perception of cough severity.^26^ The MCSQ has a 1 week recall period and items with 7-point Likert scales. It has two domains (frequency and intensity), and its domain and total scores range from 0 to 6, with higher scores indicating worse cough severity. The MCSQ will serve as a secondary outcome measure and be assessed for its measurement properties.

#### Cough Severity Visual Analogue Scale

The CS-VAS asks patients to mark their cough severity over the last week on a 100-mm VAS ranging from 0 (no cough) to 100 (worst possible cough).^27^ The CS-VAS will serve as a secondary outcome measure and support construct validation of the MCSQ.

#### Leicester Cough Questionnaire

The LCQ is a valid and reliable 19-item instrument that assesses cough impact on quality of life.^28^ The LCQ has a 2-week recall period and items with 7-point Likert scales. It has three domains (physical, psychological and social), and its domain scores range from 1 to 7, with higher scores indicating better cough quality of life. Its total score ranges from 3 (maximal impairment) to 21 (no impairment). Its minimal important differences are 1.3 (LCQ total), 0.8 (physical domain), 0.9 (psychological domain) and 0.8 (social domain).^29^ The LCQ will serve as a secondary outcome measure and support construct validation of the MCSQ.

#### Patient Global Impression of Change and Patient Global Impression of Severity Instruments

The Patient Global Impression of Change (PGIC) assesses patient-reported change at follow-up visits. We will have separate PGIC instruments for cough severity, cough intensity and cough frequency. The PGIC scores changes using a 7-point scale (ie, cough severity: +3=very much better, +2=much better, +1= a little better, 0=no change, −1=a little worse, −2=much worse, −3=very much worse). The PGIC will support construct validation and estimation of the minimal important difference of the MCSQ.

The Patient Global Impression of Severity (PGIS) assesses the patient’s overall perception of the current severity of their cough at each study visit. Separate PGIS instruments will be administered for cough severity, cough intensity and cough frequency. Responses are rated on a 5-point scale ranging from none, mild, moderate, severe and very severe.

#### EuroQol-5 Dimensions-5 Levels

The EuroQol-5 Dimensions-5 Levels (EQ-5D-5L) represents a generic health-related quality of life measure that assesses how a person’s health impacts their quality of life.^30^ The ‘5-Dimension’ refers to the five key areas of health including mobility, self-care, usual activities, pain/discomfort and anxiety/depression. The ‘5-Level’ indicates that each dimension has five levels of severity, ranging from no problems to extreme problems. The EQ-5D-5L will support a cost-effectiveness analysis of the study interventions.

### Data collection

Source documents and electronic case report forms (eCRFs) in REDCap will record all data collected during study visits.

### Withdrawal of study participant

Participants can withdraw from the study at any given time. If a participant stops study treatment, we will strongly encourage participants to attend follow-up visits for collection of outcome data. They will remain eligible for financial compensation based on their continued participation in follow-up assessments, regardless of treatment discontinuation or adherence. If they do not wish to participate in outcome data collection and wish to withdraw from all parts of the study, their anonymised data recorded up to the point of withdrawal will be included in the study analysis. All patient data will be anonymised.

### Sample size

We will enrol 124 patients and randomise them in a two-stage process. First, a 1:1 randomisation will assign patients to low-dose morphine or pregabalin (62 per group). Within each arm, a second independent 1:1 randomisation will assign patients to CCT or no CCT. This will result in four groups of 31 patients each. We powered the study on the 62-patient comparisons (ie, morphine vs pregabalin; CCT vs no CCT) rather than on individual groups. Because we anticipate a smaller effect size for the morphine versus pregabalin contrast, we conservatively based our sample size on this comparison.

The primary outcome is the change from baseline in natural log-transformed 24-hour cough frequency at 6 weeks. Assuming a 30% relative reduction in 24-hour cough frequency^31^ (corresponding to a mean difference of −0.357 units on the log scale), an SD in log coughs/hour of 0.6,^32^ and a 10% dropout, a total sample size of 124 participants (62 per intervention comparison) will provide 80% power at a two-sided alpha of 0.025. To maintain a family-wise type I error rate of 5% across our two co-primary hypotheses (morphine vs pregabalin and CCT vs no CCT), we applied a Bonferroni correction and set the significance level at α=0.025 for each comparison. We performed these calculations using the pwr.t.test function in the pwr package in R studio V.4.3.1 (Posit Software, PBC; Boston, MA, USA).

While our primary interest lies in estimating main effects, the factorial design also permits exploration of potential interactions between treatments. For the sample size calculation, we assumed no significant interaction—that is, that the effect of one intervention is consistent across levels of the other. Under this assumption, we will estimate the effect of morphine versus pregabalin by averaging across CCT and no CCT arms, and the effect of CCT versus no CCT by averaging across morphine and pregabalin arms.

To ensure sufficient participant enrolment, we will monitor recruitment at each site monthly and enact strategies (eg, additional sites) as needed to achieve the target sample size.

## Statistical analysis

### General considerations

A statistician will conduct all analyses. Descriptive statistics (count and percentage for categorical variables and mean or median with SD or IQR for continuous variables, as appropriate) will describe baseline characteristics of enrolled patients.

### Main efficacy analysis at 6 weeks

The primary and responder analyses of all primary and secondary outcomes will occur in the intention-to-treat population, which includes all participants in the group to which they were randomised. Online supplemental file 5 summarises the statistical analysis plan.

### Primary analysis of the primary outcome at 6 weeks

For the primary outcome at 6 weeks, we will use a linear model to estimate changes from baseline in log-transformed 24-hour coughs per hour. The model will include treatment group, site and baseline log-transformed 24-hour cough frequency as fixed effects. Each primary hypothesis (morphine vs pregabalin; CCT vs no CCT) will be tested at a two-sided alpha of 0.025.

We will handle missing data under a missing-at-random assumption using multiple imputation. If ≥15% of outcome data are missing, we will perform a missing-not-at-random (MNAR) sensitivity analysis using a pattern-mixture model. Missing outcomes will be assumed to differ by a fixed offset (eg, 10%) from observed values, and the impact on treatment effects will be examined. Model assumptions (ie, normality, homoscedasticity) will be checked.

Mean changes from baseline in log-transformed 24-hour coughs per hour will be estimated as marginal means with their 95% CIs, and between-group differences (95% CI) will be calculated. To present geometric means of 24-hour coughs per hour for treatment groups at each time point, we will back transform the log-transformed estimates. The percent difference in the change from baseline and 6 weeks between treatment groups will be calculated as 100*(e^diff^−1), where diff represents the between-group difference on the log scale. P values for treatment effects at 6 weeks will be reported.

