### Randomisation, allocation concealment and blinding

Authorised research staff will use an automated centralised randomisation system on Research Electronic Data Capture (REDCap) to ensure concealed allocation stratified by site and sex and with variable block sizes. The REDCap randomisation module will generate and conceal the allocation sequence, and research staff enrolling participants will not have access to the sequence prior to assignment. This is an open-label trial in which participants, study staff, investigators and treating clinicians will be aware of treatment assignment after allocation.

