#### Testing the impact of including site as a random effect

To assess potential clustering by site, we will repeat analyses for the primary and key secondary outcomes using a model that treats site as a random effect. As site represents a stratification variable in the randomisation, we do not anticipate that site-level variation will meaningfully impact treatment effect estimates. However, this sensitivity analysis will account for any unmeasured heterogeneity across sites that may influence outcomes. We will compare estimates with those from the fixed effect model to assess any meaningful differences.

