### Subgroup analysis

#### Testing whether the effect of CCT differs depending on neuromodulator treatment

Although not powered to detect interactions, we will conduct an exploratory subgroup analysis evaluating whether the effect of CCT differs depending on the neuromodulator treatment and vice versa.

Linear models will include fixed effects for site, CCT, neuromodulator treatment, their interaction and baseline log 24-hour cough frequency. Secondary outcomes with repeated measures will use mixed-effects models with participant-level intercepts and interaction terms as appropriate. If we observe evidence of a clinically meaningful interaction, treatment effects will be presented stratified by the interacting factor and conclusions will be interpreted accordingly. Interaction effects will be interpreted cautiously as exploratory.

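### The primary model omits sex, a stratification factor, and leaves its single treatment term undefined for two factorial hypotheses; naming sex and both factors is a free improvement

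*Protocol article*

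**What the plan says.** Four places in the protocol article bear on the point.

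- *Randomisation, allocation concealment and blinding* promises "concealed allocation stratified by site and sex and with variable block sizes".
- *Primary analysis of the primary outcome at 6 weeks* fixes the covariates: "The model will include treatment group, site and baseline log-transformed 24-hour cough frequency as fixed effects". The next sentence adds: "Each primary hypothesis (morphine vs pregabalin; CCT vs no CCT) will be tested at a two-sided alpha of 0.025". The article does not say how the treatment term is coded for these two hypotheses.
- *Testing the impact of including site as a random effect* refers to the design when it discusses site: "As site represents a stratification variable in the randomisation". Sex has the same status in the randomisation and is not mentioned.
- *Testing whether the effect of CCT differs depending on neuromodulator treatment* is the only place where both factors are written out: "Linear models will include fixed effects for site, CCT, neuromodulator treatment, their interaction and baseline log 24-hour cough frequency". Sex is missing there too.

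The continuous secondary and responder models repeat site and an undefined treatment term, again without sex. *Sample size* and *Discussion* say that each main effect is averaged over the other factor under an assumption of no interaction. Neither says whether the other factor is in the model.

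**The concern.** Stratified allocation makes the arms more alike on the stratifiers than chance would. If a stratifier predicts outcome and the model leaves it out, the estimated standard error does not reflect that balance. It is too large, and the test is conservative. Site is handled correctly and sex is not.

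The second part concerns the factorial structure. The treatment term can be read as one factor at a time, as both main effects, or as the four-level allocation. The first reading leaves the other factor's effect in the residual. The third admits an interaction that *Discussion* says the primary analysis assumes away. The readings can give different standard errors and p values, so the confirmatory model is not uniquely fixed. *Sample size* expects the drug contrast to be the smaller effect, so the comparison that set the sample size is the one exposed to the larger omitted factor.

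**Working it through.** **Inputs from *Sample size*.** Log difference δ = 0.357 ("corresponding to a mean difference of −0.357 units on the log scale"), SD 0.6, two-sided α = 0.025, 80% power, 10% dropout, 62 per level of each factor.

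**The plan's own figure.** An unadjusted two-sample t-test needs 54.97, so 55 per group. 55/0.90 = 61.1, so 62 per group and 124 in total. This reproduces "a total sample size of 124 participants (62 per intervention comparison) will provide 80% power at a two-sided alpha of 0.025". After dropout, m = 62 × 0.90 = 55.8 per group. The noncentrality is δ/(σ√(2/m)) = 0.357/(0.6 × 0.1893) = 3.14, and power is 80.7%. Allowing for the degrees of freedom used by site and baseline, it is 80.6%.

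**Omitted second factor, 0.6 taken as the within-cell SD.** A balanced factor with log effect b, left out, gives residual variance 0.36 + b²/4.

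| CCT effect | b | Residual SD | Variance inflation | Power, drug contrast |
|---|---|---|---|---|
| 30% (same as the drug contrast) | 0.357 | 0.626 | 9% | 76.9% |
| 41% (earlier randomised trial, *Current management of RCC/UCC*) | 0.528 | 0.655 | 19% | 72.6% |

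A simulation (112 analysed, 5 sites, blocks of 2 or 4 within site and sex, 4,000 runs per scenario, assumed log sex effect 0.2) gave 77% and 72% with CCT and sex omitted. Adding CCT alone brought power to 80% and 79%. Type I error without CCT was about 0.019 and 0.016 against the nominal 0.025.

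**Omitted second factor, 0.6 taken as the total SD.** Leaving the factor out keeps the planned 80%. Including it reduces the residual SD to √(0.36 − b²/4):

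- b = 0.357: SD 0.573, power about 84%.
- b = 0.528: SD 0.539, power about 89%.

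**Omitted sex.** The documents give no sex effect, so a log effect g of 0 to 0.4 and 70% of one sex are assumptions. Residual variance is 0.36 + 0.70 × 0.30 × g².

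| g | Variance inflation | Approximate type I error | Power (normal approximation) |
|---|---|---|---|
| 0 | 0% | 0.025 | 81.6% |
| 0.2 | 2.3% | 0.023 | 80.9% |
| 0.4 | 9.3% | 0.019 | 78.8% |

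In the simulation with g = 0.4, adding sex raised power from 78% to 81%. These losses also assume that 0.6 is the SD within sex.

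**Cost of the extra terms.** Two further degrees of freedom change power from 80.61% to 80.59%.

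**The case against.** A reader might infer that the primary analysis drops the second factor and is therefore underpowered. The text does not establish that. The sentence after the model names both hypotheses, *Trial design* speaks of four treatment combinations, and averaging over the other factor is compatible with a two-factor model. When *Discussion* says the two effects are estimated independently, it does so in the context of the no-interaction assumption and may mean only that no interaction term is fitted. The article also points to a supplemental analysis plan that is not shown and may define the term. This stands: the defect is an undefined term, not a proven omission.

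A reader might also enter the 59.3% reduction from the sponsor's cohort as the CCT effect, which would put power near 60%. *Why is this trial needed now?* describes it as a change after treatment in a small observational cohort. It is not a difference between CCT and no CCT and should not be used as one.

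The SD of 0.6 is not described as within-cell or total, so a shortfall against the planned 80% is not shown. The sample size also comes from an unadjusted t-test, and baseline adjustment may recover some precision. Finally, responder models with an identity link may fail to converge, as the article itself anticipates, and more covariates can make that worse.

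None of this explains why one stratifier is in the stated covariate list and the other is not. An article may leave detail to an analysis plan, but here the list is given and is incomplete.

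**Conclusion.** Two things hold on the text alone. Sex is a stratification factor and is missing from the stated primary model and from the article's other models. The treatment term is undefined for two factorial hypotheses.

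The consequences are conditional. Omitting sex costs nothing if it does not predict outcome, and about 3 points of power at the top of the assumed range. The second factor matters more, but only if the term means one factor at a time. Then either about 4 or 8 points are lost (within-cell SD, CCT effect 30% or 41%), or a gain of about 4 or 9 points above the planned 80% is passed up (total SD).

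In every case the error is conservative: intervals are too wide and type I error lies below nominal. The treatment estimate is not biased. This is a free improvement, not a flaw that must be fixed before the trial can be relied on.

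**What to change.** State one primary model: change in log 24-hour cough frequency on neuromodulator and CCT (both as main effects, no interaction), site, sex and baseline log 24-hour cough frequency. Take both co-primary contrasts from that one fit, each at two-sided 0.025.

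Use the same two factor terms and sex in the continuous secondary models. Use them in the identity-link responder models where those converge; otherwise use the alternative estimation that the article already allows.

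State also whether the SD of 0.6 is within-cell or total, so that the power statement can be read against the model.

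The cost is a change of wording and about two degrees of freedom. No new data are needed, since site, sex and both allocations are recorded at randomisation. Because the trial is open-label, the wording should be settled before any outcome comparison is seen.
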